### 2.8. Study procedure

Participants would visit a total 14 times for this study. The visits consist of screening, treatment and follow-up (visit 1-12), and final follow-up (visit 13) visits. The overall study schedule is presented in Table 2.

**Table 2 T2:** Study schedule and checklist for each visit.

Phase	Screening*	Treatment and follow-up												
Visit		1*	2	3	4	5	6	7	8	9	10	11	12*	13^†^*
Time		Week 1			Week 2			Week 3			Week 4			
Informed consent	●													
Sociodemographic information	●													
Medical and medication history	●	●	●	●	●	●	●	●	●	●	●	●	●	●
Physical examinations	●													
Eligibility criteria	●													
Vital signs	●	●	●	●	●	●	●	●	●	●	●	●	●	●
Randomization		●												
BMA or IDA treatment		●	●	●	●	●	●	●	●	●	●	●	●	
Visual acuity test	●	●	●	●	●	●	●	●	●	●	●	●	●	●
OSDI	●	●						●						●
VAS for subjective symptoms		●						●						●
Schirmer Ⅰ test	●	●												●
General assessment														●
Quality of life		●						●						●
Adverse events		●	●	●	●	●	●	●	●	●	●	●	●	●
Compliance assessment														●

BMA = biodegradable microneedle acupuncture, IDA = intradermal acupuncture, OSDI = ocular surface disease index, VAS = visual analog scale.

* The visits allowed to schedule on the same day = screening visit and visit 1, visit 12 and 13.

† Visit 13 is scheduled within 3 days from the time when 4 weeks passed from the visit 1.

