## 2. Method

### 2.1. Study design

This study is designed as an investigator-initiated, parallel, superiority RCT. Patients with dry eye who voluntarily agree to this study would be screened using the necessary examinations and eligibility criteria. The suitable participant would be randomly allocated to the experimental group or the control group on visit 1. The participants allocated to the experimental group would be treated with the BMA. In contrast, the participants allocated to the control group would be treated with IDA. For 4 weeks, both the groups would be treated 3 times a week (total 12 times) by each intervention. Within 4 weeks from visit 1, the investigators would conduct the final assessment after treatment termination, and the trial would be completed.

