### 2.6. Interventions

#### 2.6.1.
*The experimental group*.

The experimental group would be treated using a disposable sterilized BMA (RMD-PN1; Raphas Co. Ltd., Seoul, Republic of Korea). The basic shape of BMA is the same as a microneedle patch. Five biodegradable hyaluronic acid microneedles are attached to a hydrocolloid film (Fig. 1). The specifications of the BMA are presented in Table 1. BMA would be applied to both sides of 5 acupoints, including BL2, GB14, TE23, EX-HN5, and ST1, by Korean medicine specialists or residents who have more than 3 years of clinical experience. Attached BMAs would be removed after 4 hours. For 4 weeks, the participants would receive the treatment 12 times in total.

**Table 1 T1:** Specifications of biodegradable microneedle acupuncture.

Model name	RMD-PN1
The length of needle (mm)	1.2
The thickness of needle (μm)	<80
Array spacing (mm)	>1.4
Total length (mm)	
Width	20
Length	24
Substrate film length (mm)	
Width	16
Length	16
Weight (mg)	124 ± 12

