#### 2.8.5.
*Extra visits*.

Extra visits can be scheduled if the participants request for them or based on the investigators’ decision considering its necessity. It is allowed only if the AEs persist until the end or suspension of the trial, or if there are demands for extra follow-ups after treatment termination from the investigators or the participants. If permitted, the investigators would carry out follow-ups for the emerged AEs.

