#### 2.9.3.
*Safety assessment*.

AE includes any unintended results that occurred even though the medical device was appropriately used according to the instructions. The expected AEs of the IDA are local pain from the treated area, local bleeding from the treated area, allergic reactions of the skin, infections, localized infection symptoms (redness, swelling, and/or local pain), nausea, vomiting, headache, and/or dizziness.^[22,23]^ For the BMA, redness on the treated area, skin irritation, and/or skin erosion are also expected in addition to the expected AEs of the IDA. Investigators would check and record the emergence of AEs on the CRF at each visit.

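### Visits 12 and 13 may share a day, which leaves the 12th application with no later scheduled adverse-event check

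*Protocol article*

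**What the plan says.** Section 2.1 sets the number of treatments: "For 4 weeks, both the groups would be treated 3 times a week (total 12 times) by each intervention". Table 2 in section 2.8 places treatment at visits 1 to 12 and adverse-event recording at visits 1 to 13. Section 2.9.3 confirms the recording rule: "Investigators would check and record the emergence of AEs on the CRF at each visit". Nothing is scheduled after visit 13.

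Three statements govern the timing of visit 13:

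- Table 2, first footnote: "The visits allowed to schedule on the same day = screening visit and visit 1, visit 12 and 13".
- Table 2, second footnote, repeated in substance in section 2.8.4: "Visit 13 is scheduled within 3 days from the time when 4 weeks passed from the visit 1".
- Section 2.1: "Within 4 weeks from visit 1, the investigators would conduct the final assessment after treatment termination, and the trial would be completed".

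On wear time, section 2.6.1 says "Attached BMAs would be removed after 4 hours", and section 2.6.2 gives the same 4 hours for the control needle.

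For the control needle, section 2.9.3 lists allergic skin reactions and infection among the expected events. It then adds: "For the BMA, redness on the treated area, skin irritation, and/or skin erosion are also expected in addition to the expected AEs of the IDA".

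Section 2.8.5 allows unscheduled extra visits. Its condition begins "It is allowed only if the AEs persist until the end or suspension of the trial", and the same sentence goes on to admit requests from investigators or participants for follow-up after treatment has ended.

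**The concern.** Applications 1 to 11 are each followed by a later treatment visit at which every participant is asked about adverse events. At three visits a week this is 7/3, or about 2.3 days later on average. For application 12 the only such check is visit 13. Section 2.8.4 has that visit record what has changed since visit 12. If both fall on one day, that interval shrinks to hours at most.

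Several events that section 2.9.3 expects, such as infection, allergic reaction and erosion, can appear after the day of application. Safety is a stated aim alongside efficacy, and the Discussion (section 3) claims an advantage for the new device on allergic skin reactions. Delayed skin events therefore bear on a conclusion the trial wants to draw.

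Participants who combine the visits and those who do not are also observed differently after the last session. For the first group, later events enter the data only if someone asks for a visit. Participants know which device they received, so willingness to ask could differ by arm.

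**Working it through.** **1. The plan's own counts.** Visits: 1 screening + 12 + 1 = 14, as section 2.8 states. Treatments: 3 per week × 4 weeks = 12, as section 2.1 states. Arm size: 12/(1 − 0.20) = 15, as section 2.2 states. All three reproduce.

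**2. Can the two visits share a day?** Take visit 1 as day 0, so that week 4 is days 21 to 27. Table 2 places visit 12 in week 4. For illustration, assume visit 12 on day 25 (a Monday/Wednesday/Friday pattern; the article gives no spacing).

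| Reading of visit 13 timing | Visit 13 on | Same day possible in week 4? | Gap after a day-25 visit 12 |
|---|---|---|---|
| Up to 3 days after 4 weeks | days 28–31 | no | 3–6 days |
| 3 days either side of 4 weeks | days 25–31 | yes, days 25–27 | 0–6 days |
| Within 4 weeks (section 2.1) | by day 28 | yes | 0–3 days |

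Under the first reading the same-day permission has no effect while visit 12 stays in week 4. Under the other two it does. The article does not say which reading applies, but the footnote shows that a shared day is meant to be possible.

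**3. Extent.** At most 1 of 12 sessions per participant is affected: 1/12 = 8.3%.

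**4. Effect on participant-level incidence.** The article gives no adverse-event rates, so the risk is an assumption. Let p be the risk per session of a reaction that shows only after that day's check, constant and independent across sessions. Suppose every participant completes 12 sessions and combines the visits, and no late event is reported on demand.

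- Share with at least one delayed reaction, all 12 sessions observed: 1 − (1 − p)^12.
- Same share, only 11 sessions observed: 1 − (1 − p)^11.
- Loss: p(1 − p)^11, which is largest at p = 1/12.

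| p | 12 sessions | 11 sessions | Loss (points) | Participants per 15 |
|---|---|---|---|---|
| 1% | 11.4% | 10.5% | 0.9 | 0.13 |
| 2% | 21.5% | 19.9% | 1.6 | 0.24 |
| 5% | 46.0% | 43.1% | 2.8 | 0.43 |
| 1/12 | 64.8% | 61.6% | 3.2 | 0.48 |
| 10% | 71.8% | 68.6% | 3.1 | 0.47 |
| 20% | 93.1% | 91.4% | 1.7 | 0.26 |

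**5. Direction of bias.** With the same formulas:

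- p = 1% against 5%: the group difference goes from 34.6 to 32.7 points, so it narrows.
- p = 10% against 30%: it goes from 26.9 to 29.4 points, so it widens.

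The sign depends on rates that the article does not give.

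**The case against.** The strongest reply is that little is lost. Combining the visits is optional. If the window runs only forward from four weeks, it cannot happen in week 4 at all. Section 2.8.5 gives a route for events after treatment ends. A reaction that builds up over repeated exposure would normally have shown by visits 2 to 12, so that participant is already counted. A journal article also commonly leaves arrangements for reporting between visits to the full protocol.

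Most of this stands, and it rules out stronger readings that a reader might infer:

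- *That late reactions are lost to the safety analysis.* Section 2.8.5 lets a participant or investigator ask for follow-up after treatment, so what is missing is a scheduled check, not every means of capture.
- *That the final check takes place while the devices are still on.* The article does not say whether a same-day visit 13 comes before or after the 4-hour removal, and section 2.1 places the final assessment after treatment has ended.
- *That the gap hides harm from the new device in particular.* Both arms follow the same schedule, and the direction of bias is not determined.
- *That the size should be counted in device placements.* A count over sites and sessions says little about the comparison in section 2.10.2, which concerns adverse-event incidence between the two groups.

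The appeal to condensed reporting does not remove the point. The same-day permission is written into the current text, and an on-demand visit does not put the question to every participant.

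**Conclusion.** The point holds as a limited gap. As written, the schedule can leave the 12th application with no later scheduled adverse-event check for participants who combine visits 12 and 13. The footnote permission, the visit 13 window and the timing in section 2.1 do not fit together clearly.

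The size is at most one of 12 sessions per participant. In the model above this means at most 3.2 percentage points of participant-level incidence, under half a participant per arm. That bound rests on a constant, independent risk per session and on reading incidence as the share of participants with an event. Within that model it is a worst case, because it supposes that everyone combines the visits and nobody reports a late event. If the risk rises with repeated exposure, the loss could be larger. The adverse-event frequencies and types that section 2.10.2 also describes could miss last-session events even in participants already counted. No direction of bias can be claimed.

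The change is still worth making because it is cheap and gives every participant the same observation after the last session.

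**What to change.** Either of two changes is enough:

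- Remove visits 12 and 13 from the same-day footnote. Reconcile the wording of the visit 13 window (Table 2 and section 2.8.4) with section 2.1, so that visit 13 falls on a later day than visit 12. This guarantees only a later day. If an interval similar to that after earlier sessions is wanted, the window must say so.
- Keep the permission. Where the visits are combined, schedule one adverse-event telephone check by the existing coordinator a few days later, in both arms, and count its findings in the safety analysis.

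The cost is a line of text plus one more trip or one short call for some participants. Treatment, sample size and the efficacy analysis method are unchanged. Enrolment had already begun (section 2.13), so the change can serve only participants who have not yet finished. For the rest, the report can state how many in each arm had the two visits on one day.

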#### 2.6.2.
*The control group*.

Considering the intervention for the control group, IDA would be used with a disposable sterilized IDA needle (T-press needle DB130A; Dongbang Medical, Seongnam, Republic of Korea), also called “thumbtack needle.” A 0.18 mm × 1.0 mm-sized stainless-steel needle is attached to a small piece of paper plaster (Fig. 2). IDA would be applied to both sides of 5 acupoints, including BL2, GB14, TE23, EX-HN5, and ST1, by Korean medicine specialists or residents who have more than 3 years of clinical experience. Attached IDA needles would be removed after 4 hours. For 4 weeks, the participants would receive the treatment 12 times in total.

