#### 2.8.4.
*Visit 13*.

Visit 13 is the final follow-up visit, and would be scheduled within 3 days from the time when 4 weeks passed from the visit 1. Investigators would record the changes in the routine examinations since visit 12 on the CRF. The final assessment would be performed for the primary and secondary outcomes, including the OSDI, the VAS for subjective symptoms, the QoL, the Schirmer I test, and general assessment by the participants and investigators. Participants’ compliance for this trial would be also examined during this visit.

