BMA is based on a microneedle patch. Originally, the microneedle patch was developed in 1976 to overcome the low efficiency of transdermal drug delivery.^[31]^ It enhances drug absorption into the skin by penetrating the skin barrier with attached microneedles.^[32]^ Owing to these features, the microneedle patch has been widely applied to various fields, including pharmaceuticals, cosmetics, dermatology, and vaccination.^[30,33–38]^ Meanwhile, BMA looks similar to the conventional IDA needle upon observing their appearance. Except for the number of needles and their material, the appearance of both acupuncture needles is fundamentally the same consisting of a small needle with a needle-fixing film. Thus, the BMA can be expected to have similar therapeutic effects of acupuncture as the IDA needle, in addition to the original microneedle patch.

This study has some limitations. First, double blinding is impossible because participants can comprehend the intervention they receive based on the treated needle’s external difference. BMA has a circular translucent film, while the IDA needle has a square apricot plaster. Instead, we blinded the assessor. An investigator in charge of the outcomes assessment would be separated from contacting with the participants except for the assessment time. Moreover, a separate assessment form that cannot verify the participant’s identity is served to the assessor. Another limitation arises from the small sample size. This study recruits fifteen participants for each group. Thus, we may be unable to get the intended results. However, since this study was designed as a pilot trial, we are planning to conduct a further large-scale confirmatory clinical trial based on the results of this study.

In conclusion, the superiority of BMA possibly proven by this study could suggest new potential treatments for dry eye and the application of a microneedle patch. Furthermore, the results from this study will also serve as evidence for further large-scale BMA studies.

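### The final assessment may share a day with the 12th treatment, when worn devices can show the arm to the blinded assessor, and the visit 13 window is stated in two conflicting ways

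*Protocol article*

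**What the plan says.** **Same-day permission.** The Table 2 footnote in Section 2.8 states: "The visits allowed to schedule on the same day = screening visit and visit 1, visit 12 and 13". In the table itself, visit 12 includes a treatment. Visit 13 holds the final OSDI, VAS, quality of life, Schirmer I and general assessment.

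**Devices.** Section 2.6.1 says "BMA would be applied to both sides of 5 acupoints, including BL2, GB14, TE23, EX-HN5, and ST1", and Section 2.6.2 uses the same points for the control device. Wear time is the same in both arms: "Attached BMAs would be removed after 4 hours" and "Attached IDA needles would be removed after 4 hours". The Discussion gives the visible difference as the reason why participants cannot be blinded: "BMA has a circular translucent film, while the IDA needle has a square apricot plaster".

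**Blinding.** Section 2.5 blinds the assessor only. Section 2.5 and the Discussion give three safeguards: separate roles for assessor, coordinator and therapist; no contact between assessor and participant outside assessments; and an assessment form without identifying data.

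**Timing of the final assessment.** Section 2.1 says: "Within 4 weeks from visit 1, the investigators would conduct the final assessment after treatment termination". The second Table 2 footnote says: "Visit 13 is scheduled within 3 days from the time when 4 weeks passed from the visit 1". Section 2.8.4 repeats that visit 13 "would be scheduled within 3 days from the time when 4 weeks passed from the visit 1". Section 2.9.2.4 also places the general assessment after the last treatment.

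**The concern.** The trial claims assessor blinding in its title, and Section 2.5 justifies it on the ground that those who deliver the treatment cannot judge its result objectively. The same-day permission works against that claim. It brings the assessor and the participant together on a day when devices have just been applied, and the devices differ in shape and colour. The safeguards act before the assessment (separate roles, restricted contact) or on paper (an anonymous form). The exposure arises during the assessment itself, when contact is allowed.

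What is at stake is the credibility of the outcomes that assessor blinding can protect. These are the ones that pass through an investigator's hands: the Schirmer strip reading, the investigator's general assessment, and the measurement of the VAS mark.

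The timing is a second and separate matter. The visit that supplies the endpoint has two different windows in one document, so a site could meet one rule and breach the other.

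**Working it through.** **1. The plan's own counts.** 3 treatments per week × 4 weeks = 12 treatments. Screening + 12 treatment visits + visit 13 = 14 visits. Both agree with Sections 2.1 and 2.8. No sample-size figure is involved.

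**2. Can the assessor meet a participant wearing a device?**
- Visits 12 and 13 may fall on one day (Table 2 footnote).
- The final assessment follows treatment (Sections 2.1 and 2.9.2.4), so on that day the order is application first and assessment later.
- Devices stay on for 4 hours (Sections 2.6.1 and 2.6.2) at 5 acupoints × 2 sides = 10 sites.
- For the midterm visit, Section 2.8.3 puts the assessments before that day's treatment. That order is not open to visit 13, which comes after the last treatment.
- Nothing in the article ties a same-day visit 13 to device removal. An assessment inside the 4-hour wear time is therefore within the rules, and the device then shows the arm.

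**3. Which outcomes are exposed?**
- Investigators measure the Schirmer strip (Section 2.9.2.3) and the VAS mark (Section 2.9.2.1), and they give one version of the general assessment (Sections 2.8.4 and 2.9.2.4).
- Participants supply the OSDI answers, the position of the VAS mark and the quality-of-life score. They already know their arm, so assessor blinding protects these little, whatever the visit day.

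**4. The visit 13 window.** Take visit 1 as day 0, week 4 as days 21 to 27, and 4 weeks as 4 × 7 = day 28. Section 2.1 then allows the final assessment up to day 28. The Table 2 and Section 2.8.4 window can be read in two ways:

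| Reading of the 3-day window | Days allowed | Also allowed by Section 2.1 | Excluded by Section 2.1 | Can share a day with a week-4 visit 12 |
|---|---|---|---|---|
| Opens at 4 weeks | 28 to 28 + 3 = 31 | 28 only | 29, 30, 31 | no day |
| 3 days either side | 28 − 3 = 25 to 31 | 25 to 28 | 29, 30, 31 | 25, 26, 27 |

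Days 29 to 31 are in conflict under both readings. Under the first, the two footnotes of Table 2 also conflict with each other, because the same-day option cannot be used with a week-4 visit 12.

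**5. Interval from last treatment to endpoint.** Assume a Monday-Wednesday-Friday pattern: days 0, 2, 4, 7, 9, 11, 14, 16, 18, 21, 23, 25. Visit 12 is then on day 25.
- Window opening at 4 weeks: 28 − 25 = 3 to 31 − 25 = 6 days.
- Window of 3 days either side: 25 − 25 = 0 to 31 − 25 = 6 days.
- Section 2.1 alone, with visit 13 on or after visit 12: 0 to 28 − 25 = 3 days.

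**The case against.** The best defence is that the same day does not mean the same 4 hours. A treatment defined by 4 hours of wear can fairly be said to end at removal, so an assessment after treatment may mean one with no device in place. The order of procedures within a day is also detail that a journal article may leave to the full protocol. Both arguments have weight. They show that unmasking is not certain, and that the lack of an ordering rule is not a fault by itself. They do not remove the point, because the article states the same-day permission outright and does not settle whether removal comes first.

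On the window, Section 2.1 is a one-sentence summary, the other two statements agree, and the gap is at most 3 days. That makes the conflict small, but it remains a conflict.

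A reader might go further in four ways that the documents do not support:
- *That assessor blinding fails at the endpoint.* Only participants assessed on a combined day while wearing devices are exposed. Their number is unknown and may be zero.
- *That marks left after removal show the arm, or that a device beside the lower lid disturbs the Schirmer strip.* Section 2.9.3 has redness among the expected events for both devices, and the article does not describe where the points lie relative to the lid.
- *That the primary result is biased by this route.* OSDI is a self-report by unblinded participants, and the Discussion already discloses that they know their arm.
- *That the varying interval favours one arm.* It is open equally to both arms. A 0-day gap also needs the reading of 3 days either side, or the Section 2.1 window.

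**Conclusion.** The point holds in a limited form. A rule that the plan states allows the blinded assessor to see the allocated device at the final assessment, and the stated safeguards do not prevent it. The size cannot be given as a number: it depends on how many of the 30 participants combine the two visits and are seen within 4 hours of application. The effect is confined to the Schirmer I reading, the investigator's general assessment and the VAS measurement. For the general assessment, the article does not say that the blinded assessor is the investigator who gives the rating. Little is added to the bias of the self-reported OSDI.

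The window conflict holds under either reading: days 29 to 31 are allowed in two places and excluded in a third. If the window opens only at 4 weeks, the same-day permission cannot be used with a week-4 visit 12. In that case the unmasking risk arises only if visit 12 slips past week 4, or if sites follow the footnote or Section 2.1 instead.

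Assumptions: visit 1 is day 0 (another day convention shifts all the days alike), visit 12 is held in week 4 as Table 2 shows, and the acupoints are on the face, where an assessor would see a device.

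**What to change.** - **Same-day option.** Remove visits 12 and 13 from the same-day footnote. Alternatively, keep the option and require that the blinded assessor carry out the visit 13 assessments only when no device is in place. Either change closes the route, and no fixed order of tests is needed.
- **Window.** Reconcile Section 2.1, the Table 2 footnote and Section 2.8.4 into one visit 13 window, and state whether it opens before or at the 4-week point. If the same-day option stays, the window must be compatible with it.
- **Claim.** Limit the assessor-blinded description to the assessor-handled outcomes, and describe OSDI, VAS marks and quality of life as unblinded self-reports.

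The cost is a wording amendment with no effect on sample size. Some participants would lose the convenience of combining two of their 14 visits, or would have to wait until the devices are off. Section 2.13 reports that enrolment has begun, so the change can help only participants who have not yet reached visit 13.
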